#### Outcomes for safety

The secondary outcome of this study is to assess the safety of RIC. Any serious RIC-related adverse events are the following: (1) inability to tolerate RIC or sham-RIC procedures leading to the suspension of the study; (2) signs of tissue or neurovascular injury caused by RIC and sham RIC operations (e.g., palpation of distal radial artery pulsation, visual inspection of local edema, erythema and skin damage, or palpation of tenderness). All adverse events will be independently determined by trained individuals of the research group who are blinded by random grouping.

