**Methods:**

This is a single-center, double-blind, and randomized controlled trial, which includes patients with Parkinson's disease with EDS. All recruited patients will be randomly assigned either to the RIC or the control group (i.e., sham-RIC) with 20 patients in each group. Both groups receive RIC or sham-RIC treatment once a day for 28 days within 24 h of enrollment. Epworth Sleepiness Scale (ESS), Pittsburgh Sleep Quality Index (PSQI), Parkinson Disease Sleep Scale-2 (PDSS-2), Parkinson's Disease Questionnaire39 (PDQ39) score scales, and adverse events, such as inability to tolerate the treatment leading to suspension of the study or objective signs of tissue or neurovascular injury caused by RIC and/or sham-RIC are evaluated at 7, 14, 28, and 90 days after enrollment.

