## Subjects and methods

### Study design

All participants will be informed of the clinical research and the requirements for giving informed consent. The research plan and informed consent form are to be approved by the regional ethics committee; the trial has been registered at www.chictr.org.cn (Registration number: ChiCTR2200058430).

Forty patients are to be randomly assigned to the intervention (“RIC”) or control group (“sham RIC group”) with 20 patients in each group. Within the 24 h of grouping, each group starts RIC or sham RIC treatment for 45 min once a day for 28 days.

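### The definition of a serious RIC-related adverse event takes in ungraded local signs and has no outcome-based criterion, and the article labels the same items inconsistently

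*Protocol article*

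**What the plan says.** The Outcomes for safety section of the protocol article makes safety the secondary outcome and defines its main event class: "Any serious RIC-related adverse events are the following". Two numbered items follow.

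- Item 1 is "inability to tolerate RIC or sham-RIC procedures leading to the suspension of the study".
- Item 2 is signs of tissue or neurovascular injury caused by the real or sham procedure. Its examples are "palpation of distal radial artery pulsation, visual inspection of local edema, erythema and skin damage, or palpation of tenderness".

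The section adds that blinded members of the research group determine all adverse events.

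The abstract treats the same material differently. Its Methods paragraph lists "adverse events, such as inability to tolerate the treatment leading to suspension of the study or objective signs of tissue or neurovascular injury", without the word serious. Its Results paragraph names the measurement of serious RIC-related adverse events as a way of assessing feasibility, which is the primary goal there, and then gives confirmation of safety as the secondary goal.

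**The concern.** In trial reporting, serious normally describes what an event led to: death, threat to life, hospitalisation, lasting disability or a comparable medical consequence. Here it is attached to a list of local findings and to intolerance. Two kinds of error follow. A minor local sign attributed to the cuff can enter the serious count, and a grave systemic event can stay out of it.

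This matters more than usual because the Sample size estimation section calls the trial a phase 1 test of safety and feasibility, says there is no earlier clinical study of RIC in Parkinson's patients, and intends the results to inform a phase 2 trial. A misclassified serious-event rate would be carried forward. The abstract also places that rate under the primary goal.

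**Working it through.** The documents state no figure for this outcome, so there is nothing to reproduce. The check is a reading of the text, with one line of arithmetic.

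**Step 1. Is the list closed?** The introductory words say what the serious events are, and two items follow. The only opening is the e.g. inside item 2, which widens the examples of local injury. It does not admit events outside local injury.

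**Step 2. Is there a threshold?** Item 2 requires that the sign be an injury caused by the procedure. It gives no grade, duration or consequence.

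**Step 3. Classify hypothetical cases by the printed definition.**

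| Case | Item met | Classed as serious? |
|---|---|---|
| Mild redness, judged to be injury caused by the cuff | 2 | Yes |
| Local tenderness, judged likewise | 2 | Yes |
| Stroke during the treatment period | Neither, unless it also meets item 1 | No |
| Admission to hospital for arrhythmia | Neither, unless it also meets item 1 | No |
| Radial pulse examined | Unclear: the abnormal result is not stated | Cannot be scored as worded |
| One patient stops sessions, trial continues | Not item 1 if read literally | No, if read literally |

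**Step 4. Compare the labels.**

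| Place | Label | Role |
|---|---|---|
| Abstract, Methods | Adverse events | Evaluated at the follow-up days |
| Abstract, Results | Serious RIC-related adverse events | Measure of the primary feasibility goal |
| Outcomes for safety | Serious RIC-related adverse events | Secondary outcome |

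The first and third rows describe the same two items at different levels of seriousness. The second and third rows give the serious count different standing.

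**Step 5. Size.** Input: 20 patients per arm (Sample size estimation). If all 20 are counted, one patient is 1/20 = 5 percentage points of the arm's rate. One patient with mild redness attributed to the cuff therefore adds 5 points to the serious rate, and one patient with a stroke that meets neither item adds 0.

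**The case against.** The best defence has three parts. First, the list covers only RIC-related serious events, and a full protocol usually holds a general definition of serious adverse events that a journal article leaves out. Second, the governing phrase in item 2 is injury caused by the procedure, so not every red mark qualifies. Third, the pulse wording and the reference to suspending the study are loose drafting whose intent can be guessed.

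The second and third parts reduce the reach of the point but do not remove it. A sign attributed to the cuff still needs no minimum severity to be serious, and an outcome should not depend on guessing the intended result. The first part would hold against a complaint that a definition is missing. Here a definition is printed, and it conflicts with the abstract.

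Some stronger readings are tempting but lack support:

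- *Events are looked for on only a few treatment days.* The abstract says that the scales and adverse events "are evaluated at 7, 14, 28, and 90 days after enrollment", and a reader might infer that nothing is captured in between. The article does not say so. It does not exclude observation at the daily sessions or recall since the last visit, and such detail is commonly left to the full protocol. Even the number of stated days that fall within treatment depends on the start: three if the first session is on day 1, two if it is on day 0. Any estimate of missed signs would rest on an assumed rate, independence between sessions and no interval capture.
- *A hospitalisation would go unrecorded.* It could be recorded, because the safety section refers to all adverse events and the abstract's list is open. What fails is its classification as serious.
- *Limb thrombosis has no place.* With local signs it fits item 2, which covers neurovascular injury.
- *Trivial marks would dominate the rate.* No passage gives an expected frequency of local signs.

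**Conclusion.** The concern holds as a defect of definition. As printed, the serious category admits local injury signs of any severity, has no criterion based on outcome, and contains two elements that cannot be scored reliably. The abstract and the safety section give the same items different labels and the serious count a different role, and these passages must be reconciled.

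The effect is 5 percentage points of an arm's rate per misclassified patient, assuming all 20 in the arm are counted. The total effect cannot be estimated from the article. The conclusion rests on the printed text being the operative definition. If the full protocol has an outcome-based definition, the article should be brought into line with it. The sample size is not affected. The point should be settled before safety data are classified, and it is inexpensive to settle.

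**What to change.** Replace the single serious category with three safety outcomes, each reported by arm:

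1. Serious adverse events by the standard outcome-based criteria (death, life-threatening event, hospitalisation, lasting disability), with relatedness judged by the blinded assessors.
2. Local signs of tissue or neurovascular injury, graded and not called serious, with a reduced or absent radial pulse named as the event in place of the examination.
3. Discontinuation for intolerance, counted for each patient rather than as suspension of the study.

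Use the same labels in the abstract's Methods and Results paragraphs and in Outcomes for safety, and state once whether the serious count belongs to the primary or the secondary goal.

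The cost is a small rewording and a slightly more detailed safety table. Treatment, visits and sample size do not change. The fix does not need a checklist completed by whoever applies the cuffs. That person may see whether the pressure is 200 or 60 mmHg, which could conflict with the blinded determination already specified.

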### Outcomes

#### Outcomes for feasibility and efficacy

The primary outcomes of this study are to assess the feasibility and efficacy of RIC from changes of ESS, PSQI, PDSS-2, and PDQ39 scores from the baselines to post-treatment on days 7, 14, 28, or 90. This study will determine (1) whether ESS, PSQI, PDSS-2, and PDQ39 can be performed in the patients and (2) the differences between ESS, PSQI, PDSS-2, and PDQ39 in patients with or without RIC. Certified therapists and assistants will collect data from the subjects and the obtained information will be used for statistical analysis.

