### Statistical analysis

Data are obtained from all patients who complete the study protocols and follow-ups. They will be analyzed by per-protocol (PP) analysis. Statistical analysis will be performed using SPSS version 19 (SPSS Inc., Chicago, IL, USA). *P* < 0.05 will be considered statistically significant. Demographics and clinical characteristics will be analyzed for descriptive statistics. Continuous and categorical data will be presented as mean values, standard deviations, number values, and percentages. Continuous variables consistent with the normal distribution will be compared by the independent samples *t*-test or ANOVA or rank-sum test. Categorical variables will be compared by chi-square testing.

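### The only defined intolerance event depends on an undefined suspension of the study, and no stated outcome counts sessions stopped early or refused by patients who stay in the trial

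*Protocol article*

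**What the plan says.** - **Safety outcome (Outcomes for safety).** The section introduces a two-item list with "Any serious RIC-related adverse events are the following". Item (1) is "inability to tolerate RIC or sham-RIC procedures leading to the suspension of the study". Item (2) is signs of tissue or neurovascular injury; its examples include loss of comfort found by examination (tenderness on palpation) as well as visible signs. The section then states: "All adverse events will be independently determined by trained individuals of the research group who are blinded by random grouping".
- **Abstract, Methods.** The same condition appears, introduced as an example: "adverse events, such as inability to tolerate the treatment leading to suspension of the study".
- **Abstract, Results.** Feasibility is to be judged by measuring serious RIC-related events.
- **Outcomes for feasibility and efficacy.** Feasibility is "whether ESS, PSQI, PDSS-2, and PDQ39 can be performed in the patients". Completion of treatment sessions is not mentioned.
- **Exposure.** Under Study design, "each group starts RIC or sham RIC treatment for 45 min once a day for 28 days". Under Interventions, each session has five bilateral inflations, to 200 mmHg in the RIC arm and at most 60 mmHg in the sham arm.
- **Analysis.** "Data are obtained from all patients who complete the study protocols and follow-ups", and the analysis is per-protocol.

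**The concern.** Item (1) is defined by an administrative consequence and not by what happens during the procedure. The consequence itself is undefined, so two assessors could classify the same patient differently.

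The section Sample size estimation describes a phase 1 test of safety and feasibility, with no earlier clinical study of RIC in Parkinson's patients, whose results are to inform phase 2. Whether patients can sit through 28 daily sessions is close to the centre of that purpose, and the contrast between 200 and 60 mmHg is where the arms might differ. If patients who cut sessions short or refuse them do not appear in any stated outcome, the trial could report favourable safety and feasibility results while partial intolerance goes unreported. Because the Abstract also uses the serious events to judge feasibility, the same gap affects both aims.

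**Working it through.** The plan has no figure to reproduce here: 20 per group comes from pilot-study rules of thumb, not from an event rate. The check is therefore mainly a reading of the definitions.

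**Step 1: item (1) under three readings of suspension.** Consider two patients, both limited by cuff discomfort and both attending follow-up. Patient A stops the procedure for good. Patient B repeatedly shortens or refuses sessions but goes on with the course.

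| Suspension refers to | Patient A | Patient B |
|---|---|---|
| the whole trial | not an event | not an event |
| the patient's participation | not an event | not an event |
| the patient's treatment course | event | not an event |

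Patient A's status depends on the reading. Patient B is missed under all three.

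**Step 2: item (2).** It requires a sign of injury, visible or palpable. Pain during inflation that resolves on deflation and leaves no visible or palpable sign falls outside it.

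**Step 3: feasibility.** One statement (Outcomes) concerns whether the scales can be performed. The other (Abstract, Results) returns to the serious events. Neither counts sessions.

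**Step 4: analysis set.** Data come from patients who complete the protocol and follow-up. Patient B may be judged a non-completer and dropped. Including everyone would not by itself solve the problem, because no defined outcome would register what happened.

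**Step 5: what this could amount to.** Inputs from the article: 20 patients per arm and 28 sessions each. Rates of partial intolerance are assumed, because the article gives none.

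- One patient in an arm: 1/20 = 5 percentage points.
- Exact (Clopper-Pearson) two-sided 95% intervals:

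| Patients counted | Rate | 95% interval |
|---|---|---|
| 0/20 | 0% | 0 to 16.8% |
| 1/20 | 5% | 0.1 to 24.9% |
| 2/20 | 10% | 1.2 to 31.7% |
| 4/20 | 20% | 5.7 to 43.7% |

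- Chance of at least one such patient in an arm, 1 − (1 − p)^20: 64% for p = 5%, 88% for p = 10%, 99% for p = 20%.
- Assumed example: 6 of 20 RIC patients each stop 10 of 28 sessions early. Sessions affected: 6 × 10 = 60. Sessions planned in the arm: 20 × 28 = 560. Share: 60/560 = 10.7%. Patients affected: 6/20 = 30%. If all six remain in the trial and continue the course, item (1) counts 0/20.

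**The case against.** A reader might infer that intolerance is a safety event only if the study is suspended. The article does not go that far. The two items define the serious tier, the Abstract offers intolerance as an example, and all adverse events are to be assessed by blinded staff. A session ended because of cuff pain could therefore be recorded as a non-serious event. This stands as a limit on the point. It does not remove the gap, because no text says that shortened or refused sessions are adverse events or that they will be counted.

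A reader might also infer that these patients are scored as having tolerated RIC. No tolerated category exists, and the per-protocol rule may exclude them instead. Either route can leave partial intolerance unreported, but the article does not say which applies.

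Suspension may well mean the patient's own treatment. Permanent stoppers would then be counted, and the problem for them is only unclear wording. A still looser reading, in which ending one session is a suspension, would catch stopped sessions; but the text speaks of the study, not a session, and that reading would place every shortened session among the serious events.

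Item (2) is wider than visible injury, since it includes palpable tenderness. Only pain with neither kind of sign is outside it.

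Finally, session logs are commonly left to the full protocol and case report forms, which are not shown. That is fair for the log itself, and its absence here is not the point. The point is that the outcomes the article does state rest on an undefined term and do not cover partial intolerance.

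**Conclusion.** The concern holds in this limited form. The one defined intolerance event rests on an undefined term that appears in both the Abstract and Outcomes for safety. On each of the three readings set out, no stated safety or feasibility outcome counts sessions stopped early or refused by patients who continue in the trial. The article supports neither the claim that lesser intolerance cannot be recorded at all nor the claim that it is scored as tolerance.

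The size cannot be taken from the article. Each uncounted patient changes an arm's observed rate by 5 percentage points; the six-patient, 60-of-560-session example and the rates of 5%, 10% and 20% are assumptions. Whether a difference between the arms would be concealed depends on how non-serious events are recorded and reported by arm, which the article does not state. The correction should be made, because tolerability of repeated sessions bears directly on the trial's stated purpose.

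**What to change.** 1. In the Abstract (Methods) and in Outcomes for safety, replace the suspension condition with a patient-level definition: the participant permanently stopped the assigned procedure because of intolerance.
2. Add a tolerability or feasibility outcome: the number of sessions stopped early or refused because of discomfort, with the number of cycles completed in each.
3. Report both by arm for all randomised patients, and reconcile this with the completers-only statement under Statistical analysis.

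These changes affect only what is counted. They alter no treatment, schedule or stopping rule. The cost is a wording change and one line per session on the treatment log. The reported tolerability may also look less favourable.

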### Sample size estimation

This is a phase 1 test measuring the safety and feasibility of RIC. Because there has not been a clinical study on RIC for Parkinson's patients, there is no data for reference at this point. Hertzog (48) suggests that 10–20 patients in each group are enough to evaluate the feasibility of a pilot study. Dobkin et al. explain that most phase 1 clinical rehabilitation pilot studies start with samples of 6–12 participants (49). Based on studies addressing the safety and feasibility of RIC, this project targets 20 patients in each group. The results of this study will be used not only to determine the safety and feasibility of RIC but also to estimate the sample size and calculate the power required for the phase 2 test in the future.

### Statistical analysis

Data are obtained from all patients who complete the study protocols and follow-ups. They will be analyzed by per-protocol (PP) analysis. Statistical analysis will be performed using SPSS version 19 (SPSS Inc., Chicago, IL, USA). *P* < 0.05 will be considered statistically significant. Demographics and clinical characteristics will be analyzed for descriptive statistics. Continuous and categorical data will be presented as mean values, standard deviations, number values, and percentages. Continuous variables consistent with the normal distribution will be compared by the independent samples *t*-test or ANOVA or rank-sum test. Categorical variables will be compared by chi-square testing.

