**Results:**

The primary goal of this study is to assess the feasibility of the treatments in patients with Parkinson's disease by measuring serious RIC-related adverse events and any reduced incidence of adverse events during the trial and to study potential efficacy, improvement of patients' excessive daytime sleepiness, quality of life-based on ESS, PSQI, PDSS-2, and PDQ39 scores. The secondary goal is to confirm the safety of the treatments.

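### The completers-only per-protocol rule excludes every patient who stops for intolerance, so the first safety outcome is zero by construction

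*Protocol article*

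**What the plan says.** The Statistical analysis section says which patients supply data and gives the analysis principle: "Data are obtained from all patients who complete the study protocols and follow-ups. They will be analyzed by per-protocol (PP) analysis". It makes no exception for safety. The same paragraph assigns categorical variables to chi-square testing.

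The Outcomes for safety section states that "The secondary outcome of this study is to assess the safety of RIC" and lists two kinds of serious RIC-related event. The first is "inability to tolerate RIC or sham-RIC procedures leading to the suspension of the study". The second is signs of tissue or neurovascular injury from the cuff. The Methods part of the abstract repeats the first event as "inability to tolerate the treatment leading to suspension of the study". The Results part of the abstract goes further and gives as the primary goal to "assess the feasibility of the treatments in patients with Parkinson's disease by measuring serious RIC-related adverse events".

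Completion means one session a day for 28 days (Study design) and assessments up to day 90 (abstract, Methods).

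**The concern.** The first safety event is defined by not finishing, and the analysis set is defined by finishing. No patient can satisfy both, so the event cannot be counted in the set that is to be analysed. Patients who stop because of arm injury, the second safety event, drop out of the analysis too. That event is not forced to zero, because an injured patient may still complete, but its count is biased downward.

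The Introduction, the Conclusion of the abstract and the Sample size estimation section all give safety and feasibility as the purpose of the trial. Sample size estimation adds that there is no earlier clinical study of RIC in Parkinson's patients to refer to, and that the results will be used to plan phase 2. A tolerability figure fixed at zero in advance could support an unearned claim that the procedure is tolerated, and would carry that error into the next trial.

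**Working it through.** **Inputs from the protocol article**

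- Allocation: "Forty patients are to be randomly assigned to the intervention" or control, 20 per arm (Study design). The arithmetic is consistent: 2 × 20 = 40. The 20 comes from pilot-study guidance, so there is no power calculation to reproduce.
- Analysis set: patients who complete protocol and follow-ups, analysed per protocol (Statistical analysis).
- Safety event 1: intolerance that leads to suspension (Outcomes for safety).

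**Input not in the article:** the rate of intolerance. I assume 1 to 4 of 20 patients in an arm (5% to 20%) to show the range.

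**Step 1: set membership.** Event 1 implies suspension. Suspension implies that the 28-day course is not completed. Non-completion implies exclusion. So the number of event-1 patients in the analysis set is 0 in each arm for any true rate.

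**Step 2: what would be reported.** If k of 20 patients stop for intolerance and all others complete, counting all treated patients gives k/20, while the completers rule gives 0/(20 − k). Intervals are exact (Clopper-Pearson) 95%. For zero events in n patients the upper limit is 1 − 0.025^(1/n). For example, with n = 16, 1 − 0.025^(1/16) = 20.6%.

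| Patients stopping (k) | All treated: k/20 (95% CI) | Completers rule (95% CI) |
|---|---|---|
| 1 | 5% (0.1% to 24.9%) | 0/19 = 0% (0% to 17.6%) |
| 2 | 10% (1.2% to 31.7%) | 0/18 = 0% (0% to 18.5%) |
| 3 | 15% (3.2% to 37.9%) | 0/17 = 0% (0% to 19.5%) |
| 4 | 20% (5.7% to 43.7%) | 0/16 = 0% (0% to 20.6%) |

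At k = 4 the upper limit under the completers rule (20.6%) barely exceeds the proportion observed among all treated patients (20%).

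**Step 3: chance of seeing the problem at all.** With true rate p and all 20 patients counted, P(at least one event) = 1 − (1 − p)^20.

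| True rate p | Expected events (20p) | P(at least one), all treated | P(at least one), completers rule |
|---|---|---|---|
| 5% | 1 | 64% | 0% |
| 10% | 2 | 88% | 0% |
| 15% | 3 | 96% | 0% |
| 20% | 4 | 99% | 0% |

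**The case against.** The best counter-argument is that the Statistical analysis section never mentions adverse events. On that view it governs only the comparison of the scales, while the Outcomes for safety section governs adverse events separately and has blinded assessors determine all of them. Nothing says that recorded events would be withheld. A full protocol or SAP, not shown here, may also define a safety set.

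Some of this stands. The investigators may well intend to report every adverse event, and the mere absence of a named safety set from an article would be no finding. But the sentence on blinded assessors says who judges events, not who is counted. The completers rule is unqualified, and the same paragraph covers categorical comparisons, the type of variable that adverse events are. The problem is a stated rule that conflicts with a stated outcome. A SAP that defined a safety set would contradict the published rule, which would still need correcting.

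A second objection is that suspension may mean a pause, so that a patient who resumed and finished would be counted. Under that reading the count is no longer strictly zero, but everyone who does not resume is still lost, and those are the worst cases. The plain reading is stopping.

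Third, safety is formally a secondary outcome. That is so in the Outcomes section, but the abstract uses serious adverse events to measure the primary feasibility goal. Finally, the intolerance rates are illustrative. They show the size of the distortion if intolerance occurs, not that it is likely.

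**Conclusion.** The concern holds. On the plain reading, one of the two defined safety events cannot appear in the analysis: 0% is reported whether 1, 2, 3 or 4 of 20 patients stop for intolerance, where counting all treated patients would give 5% to 20%. The zero follows from the two definitions alone. Only the illustrated size rests on assumed rates, and on all other patients completing. It also assumes that suspension means stopping treatment and that the completers rule applies to safety data, since the article says nothing to limit it. For the injury event the claim is weaker: a downward bias to the extent that injured patients stop. Because the trial exists to establish safety and feasibility, the rule must be corrected.

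**What to change.** Replace the single rule in the Statistical analysis section with a separate one for safety. Analyse all tolerability and adverse-event outcomes in every randomised patient who received at least one RIC or sham session, by arm, with all such patients as the denominator. State that the per-protocol set is not used for safety. Say whether suspension means a pause or a permanent stop, so that the first event is counted in one way. Keep recording adverse events after a patient stops sessions, at the day 7, 14, 28 and 90 visits that still lie ahead. Report completion out of all randomised patients.

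The cost is about one sentence in the analysis section and safety follow-up of patients who stop, at visits already scheduled. No extra patients are needed.

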### Interventions

Within 24 h of enrollment, an RIC operation is to be performed *via* bilateral limb ischemic preconditioning (Doctormate, IPC-906D, produced by Beijing Renqiao Institute of Neuroscience). Electronic tourniquet cuffs are placed on both arms. Participants in the intervention group undergo five cycles of cuff inflation to 200 mmHg for 5 min, followed by deflation for 5 min (Figure 1). In other studies, physical treatments, such as bright light therapy (35) and multidisciplinary intensive rehabilitation (36), have been applied to patients for 28 days to alleviate sleep disorders of Parkinson's disease. Additionally, RIC has been used for patients from 7 to 300 days (37–43). As the first step to determine safety, the duration of RIC in this study is decided to be 28 days. Patients in the sham-RIC group receive the same procedure except the maximum inflation pressure is 60 mmHg (40) (Figure 2).

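### Completers analysed per protocol are the only stated analysis set, so the primary between-arm comparison is not protected by randomisation; the size and direction of any bias are unknown

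*Protocol article*

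**What the plan says.** The Statistical analysis section fixes the data source and the analysis principle in two consecutive sentences: "Data are obtained from all patients who complete the study protocols and follow-ups", then "They will be analyzed by per-protocol (PP) analysis". The article names no intention-to-treat, full-analysis or sensitivity set. Significance is set at P < 0.05.

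The section on outcomes for feasibility and efficacy makes efficacy primary: "The primary outcomes of this study are to assess the feasibility and efficacy of RIC from changes of ESS, PSQI, PDSS-2, and PDQ39 scores". It specifies the comparison as "the differences between ESS, PSQI, PDSS-2, and PDQ39 in patients with or without RIC". Scores are taken at baseline and on days 7, 14, 28 and 90.

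Under Interventions, the RIC arm has "five cycles of cuff inflation to 200 mmHg for 5 min, followed by deflation for 5 min", while sham patients "receive the same procedure except the maximum inflation pressure is 60 mmHg". The section on outcomes for safety lists being unable to tolerate either procedure, to the point of suspension, as the first kind of serious RIC-related adverse event.

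Under Sample size estimation, "this project targets 20 patients in each group". The basis is pilot-study convention, and the results are also meant to support sample size and power for phase 2.

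**The concern.** Randomisation makes the two groups of 20 comparable at allocation. Completing treatment and follow-up is decided afterwards. If the reasons for not completing differ between arms and are related to how patients are doing, the completers are no longer comparable groups, and a difference in their scores mixes treatment effect with selection.

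The article itself supplies a route for this: the arms differ in cuff pressure, and stopping for intolerance is anticipated. It does not show that loss will differ.

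Three things are at stake:

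- The primary efficacy comparison would rest on a selected set.
- The per-protocol restriction is not limited to efficacy. Read literally, a patient who stops for intolerance is a safety event under the outcomes section and is absent under the analysis section. The question of whether the scales can be completed would likewise be put only to those who finished.
- Results from the selected set would feed the planning of phase 2.

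This is a choice the article states, not a detail left to a fuller document.

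**Working it through.** **The plan's own figure.** 20 + 20 = 40, and 20 lies within the 10–20 per group that the article cites for pilot studies. There is no effect size, SD, power or drop-out rate, so no power calculation can be reproduced. What follows illustrates the consequence of the analysis set.

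**Inputs.** From the article: 20 per arm, 1:1 allocation, a t-test among the listed tests, significance at 0.05 (taken as two-sided). Assumed: no true effect, outcomes with SD 1, higher score worse (the article says this of the ESS), drop-out proportion q in each arm, and correlation ρ between the tendency to drop out and a worse outcome.

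**Bias formula.** With λ(q) = φ(c)/(1 − q), where φ is the standard normal density and c its quantile at 1 − q,

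bias (RIC minus sham) = −ρ_RIC·λ(q_RIC) + ρ_sham·λ(q_sham).

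A negative value favours RIC.

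λ(0.05) = 0.1031/0.95 = 0.109; λ(0.10) = 0.1755/0.90 = 0.195; λ(0.15) = 0.2332/0.85 = 0.274; λ(0.20) = 0.2800/0.80 = 0.350; λ(0.30) = 0.3477/0.70 = 0.497.

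| Drop-out RIC / sham | ρ RIC / sham | Bias (SD) | False-positive rate (simulated) |
|---|---|---|---|
| 10% / 10% | 0.5 / 0.5 | 0 | 4.9% |
| 20% / 5% | 0 / 0 | 0 | 4.8% |
| 10% / 5% | 0.5 / 0.5 | −0.5 × (0.195 − 0.109) = −0.04 | 4.9% |
| 20% / 5% | 0.5 / 0.5 | −0.5 × (0.350 − 0.109) = −0.12 | 6.9% |
| 20% / 0% | 0.5 / 0.5 | −0.5 × 0.350 = −0.17 (−0.175 before rounding) | 8.1% |
| 30% / 5% | 0.7 / 0.7 | −0.7 × (0.497 − 0.109) = −0.27 | 12.3% |
| 15% / 15% | 0 / 0.5 | +0.5 × 0.274 = +0.14 | not tabulated |

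Simulation with 20 per arm agrees with the formula to about 0.01 SD. With nobody removed, bias is 0 and the false-positive rate is 5% at any ρ. For scale, the standard error of the difference at 20 per arm is √(2/20) = 0.32 SD.

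**Precision.** Effect detectable with 80% power, two-sided 5% t-test:

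- 20 and 20 analysed: 0.91 SD
- 16 and 20: 0.97 SD
- 16 and 19: 0.98 SD
- 16 and 16: 1.02 SD

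The normal approximation, (1.960 + 0.842) × √(1/n₁ + 1/n₀), gives slightly smaller values: 0.89 SD at 20 and 20, and 0.99 SD at 16 and 16.

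**Safety, read literally.** If 4 of 20 RIC patients stopped for intolerance, the randomised set would show 4/20 = 20%. The completer set would show 0/16.

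**The case against.** The strongest defence is the trial's purpose. Sample size estimation describes a phase 1 test of safety and feasibility, the abstract speaks of potential efficacy, and there is no power basis to damage. Sixteen per group would still lie within the cited 10–20 range. This stands as a reason to lower the severity. It does not justify completers as the sole set, because efficacy is a named primary outcome, is tested for significance and will inform phase 2.

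A reader might go further in four ways that the documents do not support:

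- **That the analysis favours RIC.** It is reasonable to expect 200 mmHg to be harder to tolerate than 60 mmHg, but the article gives no comparative tolerability or drop-out data. If RIC patients leave for discomfort unrelated to sleepiness and sham patients leave because they are not improving, the bias runs the other way. With equal loss of the same kind, or loss unrelated to outcome, there is essentially none.
- **That one missed session, or a missed day 90 visit, removes a patient entirely.** This is the strictest literal reading. No adherence threshold is given, and a fuller protocol may define completion.
- **That a biased effect will be the phase 2 planning value.** The article says only that the results will be used to estimate sample size and power.
- **That groups will fall below 20.** They do so only if someone drops out, and 1.02 SD requires four losses in both arms.

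**Conclusion.** The concern holds as one about the analysis set. Per-protocol completers are the only stated population for a randomised comparison that the article calls primary, and that comparison is not protected by randomisation. As worded, the restriction also conflicts with counting intolerance as a safety event.

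The size and direction of bias are unknown. In the scenarios examined it runs from about 0.14 SD against RIC, through zero, to about 0.27 SD in its favour with a false-positive rate near 12%. These figures rest on assumed drop-out rates and correlations and are not bounds. The loss of precision is modest: from 0.91 SD to 0.97–0.98 SD if about four are lost in RIC and none or one in sham, or to 1.02 SD if four are lost in each arm.

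This should be fixed, but in a small phase 1 pilot it is not grounds for treating the trial as invalid.

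**What to change.** - Make the main efficacy analysis all randomised patients by assigned arm, using every available day 7, 14, 28 and 90 score. A repeated-measures model is one suitable choice. It is valid if data are missing at random, so on its own it does not guarantee removal of the outcome-related loss illustrated above.
- Continue the scheduled questionnaires after a patient stops sessions. This addresses the problem most directly, and scores that were never collected cannot be recovered later.
- Report safety, feasibility, completion and reasons for stopping by arm in all randomised or treated patients.
- Define completion, and keep the per-protocol analysis as a sensitivity analysis.

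The cost is a change of analysis wording, slightly more follow-up work and an estimate that may be less favourable to RIC. No extra patients are needed and the intervention is unchanged.
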